## Abstract

Completing cognitive and motor tasks simultaneously requires a high level of cognitive control in terms of executive processes and attentional abilities. Most of the daily activities require a dual-task performance. While walking, for example, it may be necessary to adapt gait to obstacles of the environment or simply participate in a conversation; all these activities involve more than one ability at the same time. This parallel performance may be critical in the cognitive or motor load, especially for patients with neurological diseases such as Parkinsonian Syndromes. Patients are often characterized by a crucial impairment in performing both tasks concurrently, showing a decrease in attention skills and executive functions, thus leading to increased negative outcomes. In this scenario, the accurate assessment of the components involved in dual-task performance is crucial, and providing an early specific training program appears to be essential. The objective of this protocol is to assess cognitive and motor components involved in dual-task performance and create a training program based on ecological activities focusing on executive and motor functions. Thus, we will employ Virtual Reality to provide semi-immersive, multisensory, ecological, standardized, and realistic experiences for rehabilitative purposes in patients with Parkinsonian Syndromes, considering its high prevalence in aging and the incidence of motor and cognitive dysfunctions in this population. Moreover, we propose to integrate the great amount of different data provided by dual-task and Virtual Reality system, using machine learning techniques. These integrations may increase the treatment’s reliability in terms of better prognostic indexes and individualized training.

## Introduction

One of the most important challenges that social and health systems are facing today is linked to the phenomenon of population aging. The current conditions underline the importance of responding to the constant increase in elderly demand, suggesting new solutions to the problems deriving from the physiological condition of older people, in an effort to better meet their requirements [1,2]. Aging could be often related to impairments in motor and cognitive functioning, which can affect various aspects of daily life depending on the degree of decline, with a consequent possible impact on the quality of life. Although the cognitive and motor aspects have always been treated as separate entities, recent literature has highlighted a relationship between these two aspects, underlining the importance of coordinated interventions to cope with the risks deriving from both impairments [3]. An example of this strong association is locomotion. Locomotion is seemingly a mechanical task, but it couldn’t be reduced to an easy action composed of a series of repeated movements. This action involves the need to simultaneously manage gait performance and one or more cognitive tasks, depending on environmental variability [4,5]. In daily-life activities, it may be necessary to adapt our gait to the obstacles of the environment or simply participate in a conversation; all these activities require us to perform simultaneous tasks. These examples highlight how a complex set of tasks are involved simultaneously in everyday motor abilities. Prupetkaew and colleagues (2019) [6] also conducted research examining the effect of cognitive and motor demand in a free-living environment and they observed alteration of motor patterns while using a phone simultaneously.

A crucial factor in motor performance are executive functions, as highlighted by recent literature [7]. Patients with Parkinsonian Syndromes provide an example of this relationship since they have a significant impairment in their movement capacity effectively and spontaneously [8], a process that is supported by a cognitive load on executive functions. Moreover, evidence stresses the relationship between aging and an altered pattern in terms of motor abilities and cognition that may be affected by different routine abilities with a possible consequence on the quality of life [8]. It is worth mentioning that motor impairments are one of the prevalent features among older adults with neurological disease and one of the most predictors of negative motor outcomes such as falls [3–9]. An increase in the risk of falls derives from the difficulty of carrying out both, motor and cognitive tasks simultaneously, a skill that could be compromised in people who often show a decrease in attention and executive functions [5–10]. In fact, since its initial description, the clinical diagnosis of Parkinsonian Syndromes has primarily focused on motor syndrome. However, nonmotor manifestations are present in most patients and can often predominate the clinical presentation. Moreover, although the rate of progression varies, it is typically quicker in people with late onset and who develop the postural instability gait difficulty form of the disease [11]. *Based on these clinical differences we decided to not consider the early onset of disease*.

A sensitive method for detecting the effect that cognitive load has on gait is the so-called dual-task (DT) paradigm [3], i.e. walking/cycling while performing a secondary task. In recent years, executive function, a crucial cognitive resource for peak performance, has recently evolved into the standard method for evaluating the relationship between cognition and motor skills [12,13]. Executive functions are integrative functions that include both cognitive and behavioural components necessary for effective, targeted actions and to control attentional resources, which are necessary to manage the autonomous activities of daily life [5]. According to recent studies, the DT strategy also seems to be a successful method for concurrent intervention on both cognitive and motor performance [14,15]. In particular, the important contribution of high-order cognitive systems in motor control would make the DT an effective training for reducing risks deriving from ineffective motor patterns. Many studies highlighted the positive potential of combined interventions in decreasing motor difficulties, global function, activity of daily life, and mood in healthy aging and patients [16,17], but further research is needed.

Virtual reality (VR) appears as a powerful tool for the assessment and rehabilitation of aging, and several tools have been successfully created [18–21]. VR is an innovative technology that artificially simulates lifelike experiences to provide users the genuine impression of being inside the real-world [22]. Objects are also depicted in a dynamic, consistent, and accurate realistic way enabling both monitoring of laboratory measurements and naturalistic observation of actual conditions. The possibility to reproduce ecological, realistic, and life-like environments and to create engaging and motivating situations for patients, leads to higher acceptance and adherence rates providing better rehabilitation results. VR can be distinguished as non-immersive, semi-immersive, and immersive according to the device employed during the interaction. Simpler technology, such a desktop PC, employs non-immersive methods to show environments on a single screen; semi-immersive technologies, like the cave automatic virtual environment (CAVE) or large screens, surround the viewer with colossal projections on the walls or screens; fully immersive devices, like Head Mounted Displays (HMDs), for example, are completely immersive systems that separate the user from external world stimuli and offer a full simulated experience, complete with a stereoscopic picture that responds to the user’s head motions [23]. We decided to structure this intervention through CAVE. This technology, among the different types of virtual reality, is a tool that makes it possible to achieve a good level of immersiveness and at the same time allows the motor domains to be stimulated as well. This possibility could be not as easy with wearable virtual reality tools such as the visor. As suggested by Riva and colleagues [24], individuals may benefit from the VR experience and increase their engagement which may determine better outcomes, throughout challenging and interactive tasks. The use of VR for cognitive and motor rehabilitation has already been widely demonstrated by neuroscientists suggesting that it is an appropriate approach in the field of rehabilitation in aging. It has been employed in the past years in motor training with positive results on gait and cognition [25–27], and many different types of interventions are used among neurological patients [21], however, most of them were focused exclusively on gait performance (e.g. strength training and balance exercise). This gap in the research opens new opportunities to develop innovative and standardized training tapping both motor and cognitive aspects simultaneously by means of new technological devices. Furthermore, by providing the patient with immersive tasks, they could have multisensory, ecological, standardized, and realistic experiences during the training.

Another important goal in the recent panorama is the issue of personalization. The possibility to customize interventions based on the specific patients’ need is the aim of the growing scenery in medicine. An increasing number of studies recommend a personalized approach instead of a standard procedure that considers patients in their homogeneity whereas each one is unique despite its pathology [28,29]. To respond to the demand of cutting-edge requirements, we propose a novel approach to forecast which motor or cognitive indicators are most revelatory of long-term maintenance of any improvements obtained. The aim is to verify whether the proposed treatment can be effective in the population according to their clinical characteristics. Estimating the treatment effect, the so-called Treatment Effect Prediction (TEP), is crucial in disease management because it ensures that patients receive the expected clinical outcomes [30]. Machine Learning (ML) techniques offer a great opportunity; they may allow the selection of the most predictive variables, which will be empirically verified via follow-up, also improved based on the historical data of patients, results of neuropsychological traditional tests, and the information provided by the VR system. Using DT tasks, clinicians dispose of a great amount of data compared to a single one, concerning different cognitive indexes and motor variables; additionally, using VR System, allows combining complex tasks providing an even greater amount of data. Thus, a linear approach could be not sufficient, and it may be necessary a multivariate approach, such as ML. ML may be more informative thanks to data fusion, integrating data in a nonlinear model which proves information about treatment prediction. Data from the cognitive, motor, and DT assessment initial evaluation can be compared to ML clinical data and the great amount of features detected during the combined VR intervention to see whether and how patients’ baseline state influenced and predicted rehabilitation outcomes.

The main aim of the present protocol is to create and validate a VR-based program for patients with motor and cognitive impairment. To assess cognition and physical aspects we propose a specific neuropsychological battery, described below. The secondary aim is to improve the quality of life in a sample of older adults with Parkinsonian Syndromes [31], preventing negative outcomes.

## Experimental design

The protocol aims to improve motor and cognitive deficits in patients with Parkinsonian Syndromes. A clinical examination will verify the inclusion and exclusion criteria. The eligible subjects will be assessed, and outcome measures will be collected (t0) by a trained physiotherapist and psychologist. The specialist who assesses participants will not train them. Patients will be then randomly assigned to a control or experimental group using a randomization sequence obtained from the website randomizer.org. The first group will complete the treatment as usual (TAU). Usually, training consists of a series of neuropsychological exercises delivered in paper and pencil modality, and classic motor activity, comprehending aerobic and anaerobic activities delivered thanks to bodyweight exercises on a stationary bike in an ordinary gym. The other one will complete a VR dual-task training protocol. Based on the evidence that exercise programs with shorter session duration and higher frequency may generate the best results [23], we propose 4–5 weeks of training of 10 sessions of 1 hour approximately, two times a week. Completed the 10 biweekly rehabilitation sessions a new assessment will be done (t1). The neuropsychological and motor assessment will be carried out before (t0), immediately after (t1) and 3 months after the end of the 10 sessions (t2) to evaluate the short/medium-term efficacy of the treatment. The chart of the trial design is presented in Fig 1. Patients must attend at least 8 out of 10 rehabilitation sessions as well as all the assessments for the treatment to be considered effective. All participants will sign the written informed consent.

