## Participants

Participants will be volunteers of both sexes, aged 65 or over (without maximum age limitation), and with Parkinsonian Syndromes as classified by Williams and Litvan (2013) [31]. The eligibility criteria will require the participants to have an MMSE [33,34] score between 30 and 24 and all participants will have normal or corrected-to-normal vision. Exclusion criteria will be invalidating internist, psychiatric, neurological conditions, presence of depression or anxiety without medications and hemianopsia or hemiplegia, severe physical or functional limitations impeding physical activity, and recurrent vertigo. The presence or absence of these criteria will be assessed during the initial clinical assessment performed by a physician. The final sample will be composed of 45 patients; to achieve this goal, at least 50 subjects will be assessed. To evaluate the size of the samples, we used a Sample Size Calculation (Power Analysis) using the software GPower*3. Based on data from Killane et al. [22], with an effect size of 0.43, alpha of 0.05, and 80% power and we estimated the minimum of subjects to be included in the rehabilitation experiment.

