## Data analysis

We will realize a mixed design trial (2x3) with population training (VR vs. TAU) as a between variable and assessment of training effect (pre-test, post-test, and follow-up) within variables. A Windows Excel sheet will be used to organize all the data related to demographic and assessment information and an identification code will be assigned to each participant to ensure anonymity of the data. A mixed ANOVA will be performed to investigate interaction effects between and within variables.

Moreover, we will analyze the accuracy during DT training to verify possible correlations with the accuracy measure in the assessment part at t0 and t1. The objective will be to examine if traditional tests reflect trained abilities.

Moreover, we will propose an innovative approach of ML in the rehabilitation field, to estimate the TEP from the collected data during the DT VR experience. Based on our research question and available data we will use a classification algorithm to create a model; we will train and test the model using data to forecast which motor or cognitive parameters are more predictive for the future maintenance of any improvements obtained, based on the model proposed by Shi and colleagues (2019) [44]. We will use one of the best programs for ML analysis, such as Python.

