## Limitation and conclusion

Limitations apply to the current work as well. CAVE systems are not as common in healthcare settings because they are expensive technology solutions and need some space. There are currently commercial solutions available at low cost, such as the Head Mounted Display (HMD), much more portable and with a greater capacity for immersion and presence. However, the CAVE among the different types of VR is a tool that makes it possible to achieve a good level of immersion allowing motor exercises without limitations. This possibility is not as easy with other VR tools, such as HMD, which could limit the users’ movements. Users wear their HMD and they do have not a complete visual of anything that happens outside the visor; this could generate feelings of apprehension and they may reduce their movements. Moreover, the CAVE offers the possibility to recreate a more realistic dual-task situation: users may view their real bicycle while cycling in a park for example, improving their engagement and immersion in the task.

Another limitation concerns the possible negative effects of using VR, i.e., cybersickness. Cybersickness is a potential result of the intensive visual and motion cuing when encountering a virtual environment, and it is defined as a set of symptoms including nausea, weariness, headache, strain, postural instability, and vomiting [58]. However, we take into account some parameters which could minimize these consequences, such as considering realistic movements to match sensory expectations, creating a clear, steady horizon environment with reference points, and limiting the time of exposure [58].

Despite some limitations, the project arises from an emerging question in the research field and aims to contribute by providing several benefits also on services and the community. On one hand, the protocol aims to ameliorate autonomy and quality of life in a sample at risk of frequent falls and cognitive impairment; on the other hand, the project might improve the Italian healthcare system by providing innovative treatment based on recent advances in neuroscientific and technological research, opening new opportunities in this field.

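### The rule tying effectiveness to 8 of 10 sessions and all assessments reads as a completer analysis, which can bias the VR versus TAU comparison in either direction

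*Protocol article*

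**What the plan says.** All references are to the protocol article.

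- **Experimental design, allocation.** Baseline (t0) is measured first, and then "Patients will be then randomly assigned to a control or experimental group using a randomization sequence obtained from the website randomizer.org".
- **Experimental design, attendance.** The same paragraph ends with the rule at issue: "Patients must attend at least 8 out of 10 rehabilitation sessions as well as all the assessments for the treatment to be considered effective". Of the three assessments, t1 (after the last session) and t2 (three months later) fall after randomisation, as do all the sessions.
- **Data analysis.** The one between-arm efficacy analysis named is a 2x3 design, arm by time: "A mixed ANOVA will be performed to investigate interaction effects between and within variables". The attendance threshold is not mentioned there, and neither are patients who miss it.
- **Participants.** "The final sample will be composed of 45 patients; to achieve this goal, at least 50 subjects will be assessed". The sample size is based on a calculation "with an effect size of 0.43, alpha of 0.05, and 80% power".
- **Limitation and conclusion.** "Another limitation concerns the possible negative effects of using VR, i.e., cybersickness". Measures to reduce it are listed, including limited exposure time.
- **Introduction, paragraph on virtual reality.** VR is expected to improve acceptance and adherence.

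Nowhere does the article say that patients below the threshold, or with a missed visit, remain in the comparison.

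**The concern.** Randomisation makes the arms comparable at the moment of allocation. If efficacy is then read only from patients who attended enough sessions and came to every visit, the groups compared have been selected by events that the treatments themselves can influence. Here the arms differ in what might make a patient stop. VR takes place in a projected virtual environment with an acknowledged risk of nausea and postural instability; TAU is paper-and-pencil work and ordinary gym exercise. The article also expects VR to hold patients better, so adherence is part of what VR is claimed to offer, and the rule would remove that difference from the comparison.

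The mixed ANOVA compounds this. In its standard form a patient with t0 and t1 but no t2 contributes nothing, although the t1 value is valid information on the immediate effect. At stake is whether a difference between VR and TAU reflects treatment or who was left in each arm.

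**Working it through.** **1. The plan's own figure.** The sample size of 45 can be reproduced in two ways:

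- Two groups, Cohen's f = 0.43 (d = 2 x 0.43 = 0.86): noncentrality f² x N = 0.1849 x 45 = 8.32; power of the F test on 1 and 43 df at 0.05 is 0.805.
- Paired or one-sample t test, dz = 0.43, two-sided: noncentrality 0.43 x √45 = 2.88; power on 44 df is 0.805.

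A two-sample d of 0.43 does not reproduce it: that needs 172 in total (two-sided). The article does not name the metric. So 45 is attainable, but a bias in SD units cannot safely be expressed as a fraction of 0.43.

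**2. Model for completer bias.** The documents give no retention rates, so everything in this step is assumed. In each arm the outcome Y is standard normal, with no true effect. A patient stays if a latent propensity L, correlated r with Y, exceeds a cut-off set so that a proportion p is retained. Then

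- mean of L among those retained: λ(p) = φ(z) / p, where z is the (1 - p) normal quantile;
- bias, VR minus TAU = r x [λ(p_VR) - λ(p_TAU)].

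Values: λ(1.00) = 0; λ(0.95) = 0.1031/0.95 = 0.109; λ(0.90) = 0.1755/0.90 = 0.195; λ(0.85) = 0.2332/0.85 = 0.274; λ(0.80) = 0.2800/0.80 = 0.350.

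Every row below has 10% overall loss with equal arms, matching 45/50 if the 50 are those randomised. Positive values favour VR, with a higher score taken as better.

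| Retained, VR / TAU | Difference in λ | r = 0.3 | r = 0.5 | r = 0.7 |
|---|---|---|---|---|
| 90% / 90% | 0 | 0 | 0 | 0 |
| 85% / 95% | 0.166 | +0.050 | +0.083 | +0.116 |
| 80% / 100% | 0.350 | +0.105 | +0.175 | +0.245 |
| 95% / 85% | -0.166 | -0.050 | -0.083 | -0.116 |

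**3. Effect on the test.** Simulated two-sided type I error at nominal 5% (25 per arm before loss, 20,000 replicates, single-visit comparison):

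| Retained, VR / TAU | r = 0.5 | r = 0.7 |
|---|---|---|
| 90% / 90% | 5.0% | 5.0% |
| 85% / 95% | 6.2% | 6.4% |
| 80% / 100% | 8.9% | 12.9% |

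**4. Change from baseline.** The figures above are for the score at one visit, whereas the planned test is the arm-by-time interaction. If L correlates r0 with the t0 score and r1 with the later score (equal SDs), the bias on change is (r1 - r0) x [λ(p_VR) - λ(p_TAU)]. With r0 = r1, meaning dropout follows a stable level, it is zero. With r1 = 0.5 and r0 = 0.3 in the 85% / 95% case it is 0.2 x 0.166 = 0.033 SD instead of 0.083. The table therefore overstates the bias on the interaction to the extent that dropout tracks baseline level.

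**The case against.** **The sentence does not name an analysis set.** It could be a clumsy statement of the minimum training thought to count as treatment. That is a possible reading, and the Data analysis section does not repeat the threshold. But attendance cannot make a treatment effective. The sentence also requires all assessments, which have nothing to do with dose. Completer analysis remains the natural reading, and the sentence needs correcting on either one.

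**Analysis sets and missing data are commonly left to the full protocol or SAP.** Silence alone would not be a finding. The point rests on the stated rule; the mixed ANOVA and the reference to a final sample only fit with it. That the ANOVA drops incomplete patients is its usual behaviour, not something the article says.

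**A reader might infer that the rule inflates the VR effect.** The documents do not support a fixed direction. Cybersickness points to selective loss from VR, but the article lists steps to limit it, excludes recurrent vertigo, and expects better adherence with VR, which would put more loss in TAU.

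**A reader might infer larger shifts.** Losing exactly the worst 10% or 20% of the VR arm raises its mean by 0.195 or 0.350 SD. The arithmetic is right, but it requires loss determined wholly by outcome (r = 1) and no selective loss in TAU. Dividing these by 0.43 assumes a two-sample d, which does not reproduce 45.

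**The allowance for loss is uncertain.** The 50 are described as assessed, and assessment precedes randomisation, so they may be screened rather than randomised patients. The 10% loss is one reading, not a stated allowance.

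**Conclusion.** The concern holds as a stated rule that can bias the trial's central comparison. Read naturally, the protocol judges efficacy in adherent completers, and nothing in the article keeps the other randomised patients in the comparison.

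Under the assumed 10% overall loss and r from 0.3 to 0.7, a ten-point retention gap between arms shifts the result by about 0.05 to 0.12 SD, and a twenty-point gap by 0.105 to 0.245 SD, towards the arm losing more patients. In the most extreme case tabulated, type I error reaches 12.9%. With equal retention and the same dropout mechanism in both arms there is no bias, and on change from t0 the bias is smaller if dropout follows a stable baseline level. These results rest on assumed retention rates, normal outcomes, poorer performers being the ones lost, and equal allocation, which the article does not state. Neither direction nor size can be fixed from the documents; that selection after randomisation is allowed can be.

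**What to change.** - Make the main analysis all randomised patients in their allocated arm, whatever their attendance, using a method that keeps partial data. A linear mixed model on all available t1 and t2 values would do; the essential point is that partial data are kept.
- Invite patients who stop training to the planned t1 and t2 assessments.
- Keep the requirement of 8 of 10 sessions and all assessments only as the definition of a secondary per-protocol set, and delete the closing clause that makes it a condition of effectiveness.
- Report retention and reasons for stopping by arm, so that readers can judge how far the two analyses could differ.

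**Cost.** Mostly wording, plus the effort of keeping patients who stop training on visits already scheduled. No new sample-size figure is needed: if 50 are randomised and all analysed, power is about 0.85 against 0.80 with 45, under the f = 0.43 reading. The small downside is that non-adherence may somewhat dilute the estimated effect.
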